### Follow-up

After assignment to the intervention or control group, it is possible that participants voluntarily leave the study, withdraw owing to medical indications, are lost during follow-up, or deviate from the protocol. These will be defined in accordance with the CONSORT statement and will be recorded in a specific format for follow-up (form: causes of withdrawal in Multimedia Appendix 10) [38]. Participants who withdraw from the interventions will be invited to answer the follow-up questionnaire at least three times via phone call.

### Data Collection

To identify the presence of neuropathic pain, the DN-4 will be used [29], which consists of ten items: 7 related to pain characteristics through an interview and the other 3 items through a clinical examination. This questionnaire, which is validated in Spanish [39], consists of descriptions and pain signs, which are evaluated dichotomously (Yes/No) in order to identify patients who have a high probability of having NP. The scores of the individual items are added together to obtain a maximum total score of 10, with a cut-off point of ≥4 (participant questionnaire in Multimedia Appendix 4).

Primary outcomes will be assessed with the Pain Catastrophization Scale (PCS) [40], the Numerical Pain Rating Scale (NPRS) [41,42], and the ASIA impairment scale [43]. The PCS is an instrument validated in Spanish for pathologies such as fibromyalgia, amputees, and patients with NP following SCI [44,45]. It inquiries about the thoughts and feelings that arise in the presence of physical pain caused by diseases, wounds, surgeries, etc. This scale has 13 items rated on a Likert scale from 0 to 4 (0=nothing at all, 1=a little, 2=moderately, 3=a lot, and 4=all time) [40,46,47]. The NPRS is a scale used in various clinical settings for multiple health conditions and measures pain intensity subjectively through a rating of 0 to 10, where 0 indicates no pain and 10 indicates the worst pain ever experienced [41,42,48]. The ASIA impairment scale is used as a universal classification tool for SCI, determining the level of sensory and motor impairment on each side of the body, single neurological level of injury, and whether the injury is complete. It will be used to quantitate sensory testing, limited by the point upon which the level and nature of SCI are present [43].

Secondary outcomes will be assessed with the Spanish version of the Quality Short-Form Health Survey, a generic scale evaluated in numerous studies [49]. This scale assesses health-related quality of life, and has been used in patients with SCIs, among other health conditions [2,50,51]. It has 36 items distributed in subscales of physical functioning, physical role, body pain, general health, vitality, social function, emotional role, and mental health. It contains Likert-type and dichotomous (Yes/No) questions with a minimum score of 0 and maximum of 100. Similarly, disability will be assessed using the World Health Organization’s Disability Assessment Schedule 2.0 questionnaire, which inquiries about difficulties that the individual has owing to a particular health condition [52]. For this study, the 12-item version will be used, which is composed up of a Likert scale ranging from 1=“no difficulty” to 5=“extreme difficulty” or “cannot do it.” The scores will be averaged for analysis [52]. In addition, sociodemographic and clinical questions will be asked for the adjustment of the analysis in a general information format (participant questionnaire in Multimedia Appendix 4). There will not be a run-in or washout period.

### Data Management, Monitoring, and Auditing

The Steering Committee (SC) is formed by the team of researchers and presided by the principal investigator. It will meet on weekly basis to analyze the therapists’ clinical notes, which will be recorded after each session of therapy from both groups in order to verify participants’ attendance, their adaptation to therapy, adverse effects, contraindications, and clinical evolution. The follow-up survey (exit survey) will be scheduled 4 weeks after the end of the therapies in both groups. Participants will be assessed twice: in a baseline survey, and in a follow-up survey at the end of the interventions. To identify the survey as baseline or follow-up, the numbers “_0” or “_1” will be used at the end of the code of each survey to indicate the type of measurement. This database will be managed in accordance with the rules of security and confidentiality of the information, which govern the health care institution and Universidad del Valle. Any serious adverse event will be assessed and classified by the Data Safety Monitoring Committee. The trial will be ended using a *P* value of <.001 as a stop boundary. There will not be any interim analysis.

### Ethics Approval

The study is endorsed by the Department of Physical Medicine and Rehabilitation, Hospital Universitario del Valle, Cali, Colombia. It was approved by the institutional review board of Universidad del Valle and Hospital Universitario del Valle (Internal Code 143-018/research ethics approval act 011-018). Additionally, the research complies with ethical standards of the Declaration of Helsinki; and in Colombia, it complies with the Ministry of Health resolution number 8430 of 1993. Since this study is considered to have “greater than minimum risk,” as it is a pilot trial where clinical interventions are conducted, there is, among other things, a risk of falls when entering and leaving the pool or a presence of fungal skin infections due to moisture. Before starting the medical evaluation, written informed consent for the study will be presented to participants by trained interviewers. These interviewers are not part of the medical assessment or randomization. Participants who agree to participate will sign the consent form, together with the required signatures of two witnesses (informed consent in Multimedia Appendix 11). Patient identities will be kept confidential, and an alphanumeric code will be used to identify each patient without enabling the distribution of personal data. The information that will be obtained in this study will be kept confidential, its use will be exclusive to the researchers, and disaggregated data will not be presented or used in a particular way that may lead to disclosure of confidential information, violation of any of the participants’ rights, or to the participants feeling stigmatized or discriminated against.

### Availability of Data and Material

Data cannot be made publicly available since that would compromise confidentiality and might reveal the identity or location of participants. Additionally, public availability of data would be in violation of the Colombian Law 1581 of 2012 and the Regulatory Act 1377 of 2013 and Article 15 of the Colombian Constitution for treatment and protection of personal data. The SC could consider those requests once the data are fully collected, and identifiers have been destroyed with approval of the institutional review board of the participating institutions. There are no contractual agreements that limit investigators’ access to data.

### Statistical Analysis

#### Sample Size and Power Calculation

In order to demonstrate recruitment feasibility, 20 participants will be enrolled (10 per group) in accordance with sample size recommendations for pilot studies [53]. As this is a pilot study, power calculations were not performed.

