**Methods:**

A sample of approximately 20 participants will be randomly assigned to either the intervention (hydrotherapy) or control group (standard physical therapy). Both interventions will be administered twice a week over a 9-week period (18 sessions in total). Primary outcomes are changes in neuropathic pain perception and pain catastrophization. Secondary outcomes are changes in disability and quality of life scores. They will be assessed at baseline and follow-up at 4 weeks after discharge. Validated Spanish language scales that will be used are the following: Numerical Pain Rating Scale, Pain Catastrophization, Health-related Quality of life, and the World Health Organization’s Disability Assessment Schedule 2.0. Generalized mixed linear models will be used for comparing baseline and postintervention means of each group and their differences, together with 95% CIs and *P* values. A *P* value of less than .05 will be considered significant.

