**Results:**

Recruitment began in April 2019, and we recruited the last participants by December 2019, with 10 individuals assigned to hydrotherapy and 8 to physical therapy (control). Results from this study will be disseminated via scientific publication, in ClinicalTrials.gov, and in national and international conferences in the latter half of 2022.

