### Primary and Secondary Objectives

The main study hypothesis is that (1) hydrotherapy is effective in reducing NP in patients with SCI. Additionally, our secondary hypotheses are that (2) hydrotherapy decreases the catastrophization of neuropathic pain, and that (3) hydrotherapy improves life quality and minimizes the degree of disability, when compared to the other physical therapy techniques.

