#### Effectiveness of the Intervention

Treatment effects will be derived using longitudinal modeling of within-person change in mean scores of the scales and subscales’ scores from baseline to follow-up. Baseline characteristics of participants in both groups will be compared using the chi-square or 2-tailed Fisher exact test for categorical variables, and the Student *t* test or Wilcoxon test for continuous variables, after assessing the tests’ assumptions. Statistical significance will be set at a 2-tailed α of .05, expressed as a 95% CI.

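### The sample is sized for recruitment feasibility and a pilot convention, but the article tests effectiveness at P<.05 and words its conclusion as comparability; 10 versus 8 participants can support neither verdict

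*Protocol article*

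**What the plan says.** All references are to the protocol article.

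- **Reason for the size** (Sample Size and Power Calculation): "In order to demonstrate recruitment feasibility, 20 participants will be enrolled (10 per group", and this "in accordance with sample size recommendations for pilot studies [53". The section adds: "As this is a pilot study, power calculations were not performed". The abstract's Methods are looser: "A sample of approximately 20 participants will be randomly assigned".
- **Main hypothesis** (Primary and Secondary Objectives): "hydrotherapy is effective in reducing NP in patients with SCI". The secondary hypotheses concern catastrophization, quality of life and disability.
- **Outcomes** (abstract, Methods): "Primary outcomes are changes in neuropathic pain perception and pain catastrophization". The secondary outcomes are disability and quality of life. The Data Collection section also lists the ASIA impairment scale among the primary instruments, though it describes it as a classification tool.
- **Decision rule** (Effectiveness of the Intervention): "Statistical significance will be set at a 2-tailed α of .05, expressed as a 95% CI". The abstract's Methods repeat the .05 threshold.
- **Recruitment achieved** (abstract, Results): "with 10 individuals assigned to hydrotherapy and 8 to physical therapy (control". The main Results section gives the same count and places recruitment between April and December 2019.
- **Conclusion** (abstract, Conclusions; Discussion, Conclusions): hydrotherapy is called a likely safe, efficient and cost-effective alternative, with results comparable to standard care. The Expected Findings section lists comparable effects on disability and quality of life.

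**The concern.** The stated reason for the sample size and the use made of the sample do not meet. Recruitment feasibility appears only as the reason for enrolling 20. It is not an objective, a hypothesis, an outcome or an analysis. What is analysed is effectiveness, by a significance test for which the sample was not sized.

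Two misreadings follow if the article is applied as written. A significant P value would be read as showing that hydrotherapy works, although at this size a difference must be large to reach significance and so is likely to exaggerate a moderate true effect. A non-significant P value, which is the likelier result unless the effect is large or the scale is very stable over time, would fit the comparability wording already in place, although failing to find a difference in so small a sample is not evidence that the treatments are alike. Meanwhile the result that a feasibility pilot exists to deliver (how fast people were recruited, how many stayed, how many attended) has no place among the outcomes.

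**Working it through.** **1. Can the planned figure be reproduced?** Only as 10 + 10 = 20. The article gives no effect size, SD, target power, dropout rate, feasibility threshold or target precision, so there is no formula to rerun.

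**2. Planned against recruited.** 10 + 8 = 18, and 18/20 = 90% of the target. A 10:8 split is possible with blocks of 4: four full blocks give 8:8, then two more assignments to hydrotherapy.

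**3. Precision, plain two-sample comparison.** Half-width of the 95% CI in SD units = t(.975, n1+n2−2) × √(1/n1 + 1/n2).

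- 10 vs 10: 2.101 × 0.447 = 0.94 SD.
- 10 vs 8: 2.120 × 0.474 = 1.01 SD.

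In this comparison an observed difference must exceed about 1.0 SD to reach P<.05.

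**4. Power, same comparison** (noncentral t, two-sided .05). The effect sizes are assumptions.

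| Assumed effect | 10 vs 10 | 10 vs 8 |
|---|---|---|
| 0.5 SD | 19% | 17% |
| 0.8 SD | 40% | 35% |
| 1.0 SD | 56% | 51% |
| 1.2 SD | 72% | 66% |

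The difference detectable with 80% power is 1.32 SD at 10 vs 10 and 1.42 SD at 10 vs 8.

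**5. Allowing for the planned longitudinal model.** The article models within-person change. If the raw SD is the same at both times and the baseline-to-follow-up correlation is r, a change score has SD = raw SD × √(2(1−r)). The half-width in raw SD is therefore 1.006 × √(2(1−r)), and the effective standardized effect is 0.8/√(2(1−r)). At 10 vs 8:

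| Assumed r | √(2(1−r)) | Half-width (raw SD) | Power for 0.8 raw SD |
|---|---|---|---|
| 0.3 | 1.183 | 1.19 | 27% |
| 0.5 | 1.000 | 1.01 | 35% |
| 0.7 | 0.775 | 0.78 | 53% |
| 0.8 | 0.632 | 0.64 | 71% |

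**6. What this means for comparability.** Even in the most favourable row, an observed difference of exactly zero leaves true differences of up to 0.64 SD in either direction inside the interval. The article states no margin within which results would count as comparable.

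**7. What the recruitment data can already say.** Counting April to December 2019 as 9 months, 18/9 = 2.0 participants per month, with an exact Poisson 95% CI of 1.2 to 3.2.

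**The case against.** The strongest reply is that the article calls itself a pilot throughout and limits its own claims. The Discussion speaks of preliminary evidence, the abstract says the trial will explore effects, and the closing paragraph leaves conclusive answers on noninferiority or superiority to later powered trials. Confidence intervals are already planned. A pilot need not have a power calculation, and the article says openly that none was done. Feasibility criteria may sit in the full protocol or analysis plan, which are not shown.

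Much of this stands: the missing power calculation is not an error, and the absence of a feasibility threshold from an article is not held against it. It does not remove the mismatch. The article does list its hypotheses, outcomes and significance rule, does not label the rule exploratory, and states comparability in the same Conclusions section that defers the question to later trials.

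A reader might also infer more than the documents support:

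- *That feasibility is the only justification for 20.* The same sentence cites a pilot-study recommendation.
- *That the planned size was not delivered, or that the shortfall is hidden.* The abstract plans for approximately 20. The count of 18, the arm split and the dates are reported, and the shortfall widens the half-width only from 0.94 to 1.01 SD.
- *That the trial says nothing about feasibility.* Recruitment numbers are given, attendance is checked from therapists' notes, and withdrawals are recorded. They are simply not made outcomes.
- *That a significant result must be an overestimate.* It is a tendency, strongest if the true effect is moderate.
- *That the planned number should be rewritten as 18, or the primary outcomes replaced by feasibility outcomes.* Either would alter the prespecified record after recruitment had closed.

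**Conclusion.** The point holds as a mismatch between the rationale for the sample size and the inference drawn from it. The sample is justified by recruitment feasibility and a pilot convention; the hypotheses, outcomes and tests are about effectiveness; the conclusion asserts comparability. With 10 versus 8, the between-group 95% CI is about ±1.0 SD in a plain comparison, or ±0.64 to ±1.19 raw SD for change scores with r from 0.8 to 0.3. Power for a 0.8 SD effect is about 35%, or 71% down to 27% over that range. Neither an effectiveness verdict from P<.05 nor comparability from a non-significant result is supported.

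These figures assume equal SDs in the arms and at both times, approximate normality, all 18 analysed, and effect sizes and correlations chosen for illustration because the documents give none. Loss to follow-up would widen the intervals. The conclusion does not turn on any one value: across the whole range the interval is too wide for a claim of comparability, and power for 0.8 SD stays below 80%.

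**What to change.** 1. In the abstract's Methods and in Effectiveness of the Intervention, label the NPRS, PCS, SF-36 and WHODAS 2.0 comparisons as exploratory estimates with 95% CIs, and remove the P<.05 rule as a test of effectiveness.
2. In the abstract's Conclusions and the Discussion's Conclusions, remove the statement that results are comparable. The matching line under Expected Findings should be brought into step.
3. Leave the planned target of 20 and the stated primary outcomes unchanged. Beside the target, state that 18 (10 and 8) were recruited, with the precision this gives.
4. Add recruitment rate, retention to the follow-up assessment and attendance out of 18 sessions as feasibility results, each with a 95% CI, and declare that they were added after recruitment. The sources are already provided for: enrolment dates and counts (Results), withdrawal forms (Follow-up) and therapists' notes (Data Management, Monitoring, and Auditing).

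The cost is wording and a few descriptive estimates from records already provided for, made before the results are published. The downside is that the trial gives up an efficacy headline.

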#### Descriptive Analysis

The categorical variables will be described in terms of frequency and percentage, and for hypothesis testing, chi-square test or the Fisher exact test will be used. Quantitative variables will be described with measures of central tendency and dispersion, and hypothesis tests based on the type of variables to be analyzed as well as the assumptions of each test.

#### Effectiveness of the Intervention

Treatment effects will be derived using longitudinal modeling of within-person change in mean scores of the scales and subscales’ scores from baseline to follow-up. Baseline characteristics of participants in both groups will be compared using the chi-square or 2-tailed Fisher exact test for categorical variables, and the Student *t* test or Wilcoxon test for continuous variables, after assessing the tests’ assumptions. Statistical significance will be set at a 2-tailed α of .05, expressed as a 95% CI.

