#### Analysis of Outcomes

An intent-to-treat analysis, which will include all study participants based on participants’ arm allocation will be used. A random effects model will be used to estimate the effect of hydrotherapy by including time points (0 = baseline, 1 = follow-up) and participant ID as random effects to account for within-person correlation across time and between-person correlation. Participants lost to follow-up will be handled using single imputation procedures on the basis of the amount of missing and their distribution.

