## Results

The first patient was enrolled in the study on March 30, 2019. The project timeline was changed owing to the COVID-19 pandemic and therefore delayed. Recruitment began in April 2019 and we recruited the final participants by December 2019. Figure 1 shows the flow diagram of the study. Participants were selected from the database of patients registered at the Spinal Trauma Clinic, Physical Medicine and Rehabilitation Unit of a Specialized Trauma Center [54]. We have collected information from 18 participants, including 10 in the hydrotherapy group and 8 in the physical therapy group. Results from the study will be disseminated via scientific publication, in ClinicalTrials.gov, and in national and international conferences in the second part of 2022. Authorship will be defined on the basis of the International Committee of Medical Journal Editors’ criteria for authorship. The authors do not have publication restrictions and will not use professional writers when reporting the results.

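### Read naturally, the outcome model is a change-score comparison; adjusting for the baseline score already collected would be more precise unless the baseline–follow-up correlation is high

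*Protocol article*

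**What the plan says.** Three places in the protocol article bear on how the treatment effect is estimated.

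- Effectiveness of the Intervention: "Treatment effects will be derived using longitudinal modeling of within-person change in mean scores of the scales".
- Abstract, Methods: the mixed models serve for "comparing baseline and postintervention means of each group and their differences".
- Analysis of Outcomes: the random effects model is fitted by "including time points (0 = baseline, 1 = follow-up) and participant ID as random effects". No fixed effects are listed, whether for arm, arm by time or a baseline covariate.

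Table 1 schedules all four outcome scales at both T1 and T2, so each participant's baseline score is available. Data Collection says that "sociodemographic and clinical questions will be asked for the adjustment of the analysis", but the baseline outcome score is not named among the adjustment variables.

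On baseline balance, Effectiveness of the Intervention says: "Baseline characteristics of participants in both groups will be compared using the chi-square or 2-tailed Fisher exact test for categorical variables", with t or Wilcoxon tests for continuous variables. The same section adds: "Statistical significance will be set at a 2-tailed α of .05".

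On numbers, the Results section reports: "We have collected information from 18 participants, including 10 in the hydrotherapy group and 8 in the physical therapy group".

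**The concern.** With two visits, a model of within-person change that gives each arm its own baseline mean compares the arms on follow-up minus baseline. That comparison subtracts the whole of any baseline difference. Adjusting for the baseline score subtracts only the part that the data show to carry over to follow-up. When the correlation is low or moderate, full subtraction adds noise.

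In a trial of 18 people the intervals are wide in any case, and the article aims at preliminary evidence of efficacy with 95% CIs. What is at stake is the width of those intervals. A related cost is the error in any one trial whose arms happen to start at different pain or catastrophizing scores.

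The baseline tests are a smaller matter. After randomisation any difference between arms is due to chance, so a P value for it answers no open question.

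**Working it through.** **Inputs.** From the document: 10 and 8 participants (Results) and two-sided 0.05 (Effectiveness of the Intervention). Assumed: baseline and follow-up SDs equal and set to 1, and a baseline–follow-up correlation ρ, which the document does not give and which is therefore varied. The plan's only size figure is 20 = 10 + 10, taken from pilot-study recommendations without a power calculation. No effect size or variance is stated, so there is nothing further to reproduce.

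**Step 1: what the model estimates.** One simulated data set (10 versus 8, ρ = 0.5, complete data) was analysed four ways:

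| Analysis | Estimate | SE |
|---|---|---|
| Mixed model, arm by time, separate baseline means | 0.612 | 0.486 |
| t-type comparison of change scores | 0.612 | 0.486 |
| Mixed model, common baseline mean | 0.700 | 0.404 |
| ANCOVA on follow-up with baseline score | 0.703 | 0.404 |

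The first two agree, and the last two are essentially the same. The result therefore turns on whether the baseline means are free or common.

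**Step 2: variances.** Let k = 1/10 + 1/8 = 0.225 and N = 18.

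- Change score: 2(1 − ρ)k, on N − 2 = 16 df.
- Baseline-adjusted: (1 − ρ²)k × (1 + 1/(N − 4)), on N − 3 = 15 df. The last factor is 1 + 1/14 = 1.071, the small-sample price of estimating the slope.
- Ratio, adjusted over change: (1 + ρ)/2 × 15/14.

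Worked at ρ = 0.5: change 2 × 0.5 × 0.225 = 0.225 (SE 0.474); adjusted 0.75 × 0.225 × 1.071 = 0.181 (SE 0.425); ratio 0.80.

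| ρ | Variance ratio | 95% CI half-width, change (SD) | 95% CI half-width, adjusted (SD) |
|---|---|---|---|
| 0.3 | 0.70 | 1.19 | 1.00 |
| 0.5 | 0.80 | 1.01 | 0.91 |
| 0.7 | 0.91 | 0.78 | 0.75 |
| 0.8 | 0.96 | 0.64 | 0.63 |
| 0.85 | 0.99 | 0.55 | 0.55 |
| 0.9 | 1.02 | 0.45 | 0.46 |

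The variances are equal at ρ = 2 × 14/15 − 1 = 0.87. The interval widths are equal at about 0.85, because the adjusted analysis also has one df fewer. With 20,000 simulated trials at each correlation, the variance ratios were 0.70, 0.80, 0.90, 0.99 and 1.04 at ρ = 0.3, 0.5, 0.7, 0.85 and 0.9. At the planned 10 versus 10 the formula gives nearly the same ratios (0.69, 0.80 and 0.90 at ρ = 0.3, 0.5 and 0.7).

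**Step 3: chance imbalance.** The SE of a baseline difference is √0.225 = 0.47 SD. An imbalance above 0.5 SD in either direction therefore has probability of about 29% for each scale (0.5/0.474 = 1.05, normal approximation). Given an imbalance d, the change score is off by (1 − ρ)d in expectation. At ρ = 0.5 and d = 0.5 this is 0.25 SD. Baseline adjustment removes this error in expectation.

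**Step 4: the baseline tests.** At 10 versus 8, a two-sample t test has about 17% power to flag a true difference of 0.5 SD. A non-significant result is therefore no evidence of balance.

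**The case against.** The strongest reply is that no sentence fixes separate baseline means. Analysis of Outcomes leaves the fixed effects open, and a common baseline mean would already recover the precision of ANCOVA. An article may leave that detail to the full protocol or analysis plan. This stands to the extent that it would be wrong to say the plan rejects baseline adjustment. But the Abstract and Effectiveness of the Intervention do describe the effect, both times as change or as pre and post means within each group. That wording points to the change-score contrast.

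A reader might infer that the planned estimate is biased. It is not: over repeated randomisations both estimators are unbiased. The error in Step 3 is conditional on the imbalance that happens to occur.

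A reader might also infer that the baseline tests will choose the covariates, because Data Collection mentions adjustment. Nothing links the two. The tests are a separate comparison of participant characteristics and do not touch the effect estimate.

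Finally, this is a pilot with no power target, and the article leaves conclusive answers to later trials. That also stands. A wider interval defeats no stated goal, so the gain is one of efficiency only.

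**Conclusion.** The point holds in a limited form. As naturally read, the effect is a change-score comparison, and adjusting for a baseline score already collected would be more precise over much of the plausible range. The variance falls by about 30% at correlation 0.3, 20% at 0.5, 9% at 0.7 and 4% at 0.8. There is no gain from about 0.85 to 0.87, and a loss of about 2% at 0.9.

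These figures rest on an assumed correlation, equal SDs at the two visits, complete data and 10 versus 8 participants. The document does not support a claim that precision is lost whatever the correlation. Follow-up comes 4 weeks after a 9-week course of treatment, so a very high correlation cannot be taken for granted either. The baseline P values are a minor matter of presentation.

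**What to change.** In Effectiveness of the Intervention and Analysis of Outcomes, define the effect for each scale as the difference between arms at T2, adjusted for that scale's baseline score. Either ANCOVA or the mixed model with a common baseline mean will do; state which, and list the fixed effects. If a common baseline mean was always intended, one sentence saying so is enough.

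Recruitment is complete and data from 18 participants are in hand, so the choice needs a dated record showing that it was made before the analyst, who is masked to allocation, was unmasked.

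Separately, describe baseline characteristics by arm without P values.

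No new data or participants are needed. The statistical price is one degree of freedom and about 7% variance inflation at n = 18, already included in the ratios above. The net loss is negligible if the correlation proves to exceed about 0.87.
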